## Abstract

**Background:**

Cognitive behavioural therapy (CBT) is an effective treatment for fatigue and disabilities in patients with chronic fatigue syndrome (CFS). However, treatment capacity is limited. Providing web-based CBT and tailoring the amount of contact with the therapist to the individual needs of the patient may increase the efficiency of the intervention. Web-based CBT for adolescents with CFS has proven to be effective in reducing fatigue and increasing school attendance. In the proposed study the efficacy of a web-based CBT intervention for adult patients with CFS will be explored. Two different formats of web-based CBT will be tested. In the first format named *protocol driven feedback,* patients report on their progress and receive feedback from a therapist according to a preset schedule. In the second format named *support on demand*, feedback and support of the therapist is only given when patients ask for it. The primary objective of the study is to determine the efficacy of a web-based CBT intervention on fatigue severity.

**Method/Design:**

A randomized clinical trial will be conducted. Two-hundred-forty adults who have been diagnosed with CFS according to the US Centers for Disease Control and Prevention (CDC) consensus criteria will be recruited and randomized to one of three conditions: web-based CBT with *protocol driven feedback*, web-based CBT with *support on demand,* or wait list. Feedback will be delivered by therapists specialized in CBT for CFS. Each of the web-based CBT interventions will be compared to a wait list condition with respect to its effect on the primary outcome measure; fatigue severity. Secondary outcome measures are level of disability, physical functioning, psychological distress, and the proportion of patients with clinical significant improvement in fatigue severity. Outcomes will be assessed at baseline and six months post randomization. The web-based CBT formats will be compared with respect to the time therapists need to deliver the intervention.

**Discussion:**

As far as we know this is the first randomized controlled trial (RCT) that evaluates the efficacy of a web-based CBT intervention for adult patients with CFS.

**Trial registration:**

NTR4013

## Background

Chronic fatigue syndrome (CFS) i.e. often also named ME (myalgic encephalomyelitis/encephalopathy) by patient groups is characterised by medically unexplained, severe, and persisting fatigue that leads to substantial disability. Following the widely used US Centers for Disease Control and Prevention (CDC) consensus criteria for CFS, patients not only suffer from fatigue for six months or longer but also report four or more of eight additional symptoms: unrefreshing sleep, post-exertional malaise, headaches, muscle pain, sore throat, multi-joint pain, tender cervical or axillary lymph nodes, impaired short-term memory, and/or concentration problems [1, 2]. A recent meta-analysis comparing the prevalence rates of CFS from studies conducted in different countries found a mean prevalence rate of about 1 % [3]. Cognitive behavioural therapy (CBT) for CFS is an effective treatment [4], leading to a significant reduction of fatigue and disabilities. A subgroup of patients fully recovers following treatment [5, 6].

The cognitive behavioural model for CFS is based on the assumption that fatigue and disability are perpetuated by fatigue related beliefs and behaviours. CBT is aimed at changing these beliefs and behaviours. Individual CBT for CFS is an intensive treatment, requiring between 13 to 16 sessions over a period of six to eight months depending on the protocol used [7–10]. Treatment capacity and budgets for delivering treatment are limited. More efficient interventions are needed to both increase treatment capacity and reduce the costs of treatment. One way of achieving this is to develop a minimal intervention for the subgroup of CFS patients who do not need intensive CBT. Our research group developed one such a minimal intervention—guided self-instruction [11]. Guided self-instruction consists of a booklet with instructions combined with fortnightly email contact with a therapist. The information and instructions in the booklet are based on the protocol for individual CBT for CFS [8]. It has been repeatedly shown that guided self-instruction leads to a significant reduction of fatigue and disabilities [11–12]. For a subgroup of about 25 to 30 % of CFS patients the level of fatigue was within normal limits following the intervention. This is less than in face-to-face CBT. Guided self-instruction was also applied in a stepped care model for CFS. Stepped care started with guided self-instruction and, if insufficient, was followed by regular face-to-face CBT. Stepped care was as effective as face-to-face CBT but more time efficient as therapists had to invest less time per patient [13].

Although guided self-instruction is effective, fewer patients benefit from this intervention than from face-to-face therapy. Further development of guided self-instruction should be aimed at improving the efficacy of the intervention without substantially increasing the time therapists need to treat a patient. A possible way of achieving this is to design a web-based version of this intervention; CBIT (cognitive behavioural Internet therapy). The Internet has proved to be an effective medium for delivering CBT in a range of disorders [14]. Online therapy for CFS in adolescents—FITNET (Fatigue In Teenagers on the InterNET)—has proved to be as effective as face-to-face CBT in adolescent CFS patients [15].

Using online platforms for therapy offers new opportunities for interaction. Compared to the booklet used in guided self-instruction, online platforms provide more ways of communication, for example chat sessions or text-alerts via sms. Assignments can be interactive and patients can be given access to interview excerpts with patients that illustrate essential elements of the therapy. Therapists can get access to and offer feedback on the completed homework of patients so that they are able to follow the progress of the patient.

Although online CBT has shown to be effective in several disorders and also in adolescents with CFS, its efficacy in adult CFS patients has not yet been shown. We developed a web-based CBT for CFS based on the guided self-instruction and will test its efficacy in the proposed study. As little is known about the optimal form and amount of feedback delivered by the therapist [16], we developed two formats of the intervention.

In the first format, patients are asked by their therapist to report on their progress by email according to a schedule. In response, the therapist offers feedback. This format is named *protocol driven feedback*. Asking patients to email regularly and providing regular feedback according to a fixed schedule makes online CBT time consuming for therapists, possibly without increasing its efficacy. Patients may also report on their progress with respect to parts of the web-based CBT they do not need therapist input for. An alternative way of providing support is to tailor it to the needs of the patient and only give feedback when the patient asks for it. We assume that this will be more time efficient—i.e., requiring less therapist time to deliver, —than giving support according to the preset schedule. We named this second format of the web-based CBT *support on demand*. The efficacy of both web-based CBT interventions will be determined by comparing each web-based CBT format to a wait list control group with respect to its effect on the primary outcome measure: fatigue severity. Subsequently, we will determine if both forms of web-based therapy lead to a reduction of disability, improved physical functioning, less psychological distress and/or a higher proportion of patients with a clinically significant improvement in fatigue compared to a wait list condition. Furthermore, the effect on treatment outcome of how and when feedback is delivered to patients will be determined in an exploratory analysis by comparing the efficacy of the two web-based CBT formats with each other with respects to its effect on primary and secondary outcome measures. We will also compare therapists’ time needed to deliver the intervention. We hypothesize that:Fatigue severity will be significantly lower at second assessment following web-based CBT compared to the wait list control group.Patients who receive web-based CBT will report significantly less disabilities and psychological distress and significantly more often show clinical significant improvement in fatigue compared to the wait list control group.Patients who received *protocol driven feedback* web-based CBT will report a significantly larger decrease in fatigue severity, level of disability, psychological distress and report more often a clinical significant improvement than patients who received web-based CBT with *support on demand*.

## Methods/Design

### Study design

The efficacy of the web-based CBT will be determined in a randomized controlled trial (RCT) with a follow-up six months after randomization (T1). All patients will start with two intake sessions with a therapist and a baseline assessment (T0), which is part of clinical routine for CFS patients referred to our CFS treatment centre. At the second intake session, eligible patients will receive written information about the study from their therapist and will be asked to participate. Eligible patients who give written informed consent will be randomized into one of three conditions (see Fig. 1):

**Fig. 1 Fig1:**
[figure not shown]
Flowchart of study

Web-based CBT with *protocol driven feedback*,Web-based CBT with *support on demand* orA wait list condition.

Patients in the wait list condition will wait for six months. After the evaluation session at T1, all patients from the wait list condition directly start with face-to-face CBT. They will not receive web-based CBT.

The primary endpoint of the study is fatigue severity at six months post-randomization (T1). Secondary outcome measures are level of disabilities, physical functioning, psychological distress, and proportion of patients with clinically significant improvement in fatigue. In the main analysis both conditions of the web-based CBT will be compared with a wait list condition with respect to the effect on fatigue severity. Subsequently, the effects of each of the treatment conditions on the secondary outcomes will be compared with the wait list control group.

#### Study population

In total 240 patients will participate in the study. All patients are referred to the Expert Centre for Chronic Fatigue (ECCF), a tertiary treatment centre for chronic fatigue of the Radboud university medical center in the Netherlands. All patients will meet CDC consensus criteria for CFS [1, 2]. They will all be severely fatigued with a score 35 or higher on the subscale fatigue of the Checklist Individual Strength (CIS). According to the consensus criteria the fatigue must be associated with significant disabilities. The latter is operationalized as scoring 700 or higher on the Sickness Impact Profile 8 (SIP8 total score). The other inclusion criteria are described in Table 1. Patients will be (temporarily) excluded when engaged in a legal procedure concerning disability-related financial benefits or when participating in other research [17]. We will assess the presence of psychiatric disorders using the MINI and clinical assessment and exclude patients who do not meet the inclusion criteria of the CDC with respect to current psychiatric disorders and/or having a medical history with psychiatric disorders.

**Table 1 Tab1:** Inclusion and exclusion criteria

1) ≥ 18 years.	
2) Able to speak, read, and write Dutch.	
3) Able to use a computer and have access to Internet.	
4) CFS diagnosis according to the CDC consensus criteria:	[1, 2]
5) Severe fatigue is assessed with the subscale fatigue severity of the Checklist Individual Strength (CIS). Severe fatigue is operationalized as scoring ≥ 35.	[23]
6) Disabilities; Disability is assessed with the total score of the Sickness Impact Profile (SIP8). Severe disability is operationalized as a total score ≥ 700 on the SIP8.	[27, 41]
7) Given written informed consent.	
Exclusion criteria	
1) Engaged in a legal procedure concerning disability-related financial benefits.	
2) Participating in other CFS research.	

#### Ethical approval

This study will be carried out in accordance with The Code of Ethics of the World Medical Association (Declaration of Helsinki) for experiments that involve humans. This study has been reviewed and approved by the Medical Ethical Committee of the Radboud university medical center (reference NL42543.091.12) and has been registered in the Dutch Trial Register (trial number: NTR4013). Patients will receive verbal and written information about the study and will be asked to sign a written informed consent form before randomization and were requested not to follow other treatments for fatigue during participation in the study. Patients will receive written information about the study results when the paper reporting on the study has been published.

#### Randomization and blinding

Patients will be randomly allocated to one of the three conditions. This web-based randomization was computer-generated by creating blocks of 12 patients. Patients are contacted one week later to ask them if they want to participate in the study. An administrative assistant will call the patient and will perform randomization during this phone call. If patients do not need time to think about their decision and decide to participate, randomization will take place immediately at the second intake session. This will be performed by an administrative assistant in the presence of the therapist and patient. After randomization, therapists and patients will be able to read the randomization result on the screen i.e. ‘1) Internet therapy’ or ‘2) Internet therapy’ or ‘wait list’. Patients will not be informed that there are two web-based CBT treatment conditions. Knowledge of the two different treatment arms could affect the behaviour of the patient while following the web-based CBT. During the second intake session the therapist will explain that the therapist will be available to support them during the web-based CBT without specifying the frequency of support. In an instruction on the first page of the web-based application, only available after randomization, participants can read how to contact their therapist and when their therapist will contact them. The cognitive behavioural therapist who performs the intake will also deliver the web-based CBT. Test assistants will do all assessments. Therapists and test assistants are not blinded with respect to condition. This will most probably not introduce a bias as there is no contact between test assistants and patients following randomization. The test assistant sends a link via email to the patient, patients will fill in the questionnaires at home.

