#### Training and supervision of therapists

The therapists delivering the web-based CBT are psychologists and cognitive behavioural therapists who are trained and experienced in delivering CBT for CFS. They will receive weekly group supervision regarding the web-based CBT. All therapists received training to improve their online communication skills with patients. The therapist will aim to write the emails in such a way that it motivates patients to follow the instructions of the intervention.

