### Sample size calculation

Based on a previous study with guided self-instructions [11] we expect a mean difference on the CIS fatigue severity score between each web-based CBT format and the wait list condition of 6.7. The standard deviation in this study at second assessment was 12.1 in the treatment condition and 8.7 in the wait list condition. In order to answer the primary objective of this study to detect a difference of 6.7 points on the CIS fatigue between each of the web-based CBT formats and the wait list condition, assuming the same standard deviations as in the aforementioned study, with a two sided alpha of .025 and a, power of .95, 76 patients are needed in each of the three conditions at T1. This number is based on a *t*-test. Because an ANCOVA with baseline assessment as covariate will be used (which increases statistical power) this sample size has been multiplied with (1–0.342^2^) [39]. The correlation between the baseline CIS-fatigue score and the score at second assessment was 0.342 in the aforementioned study. After correction 68 patients with complete data per condition are needed. Assuming a drop-out rate of 15%, based on previous trials testing the guided self-instruction [11, 12] we will have to include 80 patients in each group to have 95% power to detect the expected difference of 6.7 points on the CIS fatigue between each of the CBT formats and the wait list condition.

In an exploratory analysis we will determine whether there is a difference in efficacy between web-based CBT with *protocol driven feedback* and web-based CBT with *support on demand*. On the basis of the calculated sample size of 68 patients with complete data per treatment arm, a power of .80 and a two sided significance level of 0.05 we will be able to detect a difference between both conditions that corresponds with an effect size (Cohen’s d) of 0.48 (moderate size effect size).

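### A single fixed block size of 12, with allocations visible to the therapist who helps judge eligibility and invites the patient, leaves up to about one in six web-versus-wait-list assignments predictable if therapists pool what they see

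*Protocol article*

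**What the plan says.** All references are to the protocol article.

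- **Sequence.** Under Randomization and blinding: "Patients will be randomly allocated to one of the three conditions", and "This web-based randomization was computer-generated by creating blocks of 12 patients". No second block size and no stratification factor is mentioned. Study population places all recruitment at one tertiary centre.
- **Size.** Study population: "In total 240 patients will participate in the study". Sample size calculation: "we will have to include 80 patients in each group". The arms are therefore equal.
- **Eligibility.** Assessments says that the therapist's first intake session includes the MINI. Study population adds a judgement element: "We will assess the presence of psychiatric disorders using the MINI and clinical assessment and exclude patients who do not meet the inclusion criteria".
- **Invitation.** Study design, on the second intake session: "eligible patients will receive written information about the study from their therapist and will be asked to participate".
- **Visibility.** Randomization and blinding: "After randomization, therapists and patients will be able to read the randomization result on the screen". The same section says that therapists are not blinded and that the therapist who does the intake also delivers the web-based treatment.
- **Timing.** An administrative assistant runs the randomisation. This happens at the second intake session if the patient decides at once, and otherwise during a telephone call a week later.
- **Contact between therapists.** Training and supervision of therapists: "They will receive weekly group supervision regarding the web-based CBT".

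The article's one remark on bias from lack of blinding, in Randomization and blinding, rests on test assistants having no contact with patients after randomisation. It covers outcome assessment and not selection at enrolment.

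**The concern.** With a fixed block size and visible results, anyone who keeps a tally knows what is left at the end of each block. The person best placed to act on that knowledge is the intake therapist, who influences whether and when a patient is invited and helps decide the psychiatric exclusion. The control condition is a six-month wait, so a therapist may well have a view on which patients should not wait or which would suit web therapy. Such a view can affect invitations without any intent to interfere.

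If that happened, the arms would differ at baseline in motivation, urgency or perceived suitability. The primary ANCOVA adjusts for baseline CIS fatigue only. The article gives a correlation of 0.342 between baseline and follow-up CIS, so that covariate accounts for 0.342² = 0.117, or about 12%, of the variance in the outcome, and it would leave selection on other characteristics largely uncorrected. Both primary contrasts use the same wait-list group, so both would be affected. The primary outcome is self-reported and patients know whether they are waiting, so there is no masked measurement to offset the problem.

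**Working it through.** **The plan's own figures.** The article gives no figure for predictability. Its sample size reproduces. With a common SD of √((12.1² + 8.7²)/2) = 10.54, a difference of 6.7, two-sided alpha 0.025 and power 0.95, the noncentral t gives 76 per arm. Then 76 × (1 − 0.342²) = 67.1, rounded up to 68, and 68/0.85 = 80. Three arms of 80 make 240. The present point does not alter this.

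**Inputs.** Block size 12, three equal arms, 240 patients. Each block therefore holds 4 + 4 + 4 places, or 8 web and 4 wait-list, and there are 240/12 = 20 blocks.

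**Upper bound, web versus wait list.** Assume that the observer knows the block size and boundaries and every earlier allocation. A place is then certain once only one type remains. In a random order of a places of one type and b of the other, the expected closing run of the first type is a/(b + 1).

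- Web places at the end: 8/(4 + 1) = 1.600
- Wait-list places at the end: 4/(8 + 1) = 0.444
- Sum: 2.044 per block; 2.044/12 = 17.0%; 2.044 × 20 = 40.9, about 41 patients

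Enumerating all 495 orders gives the same value. The length of the certain run is distributed as follows:

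| Run length | 1 | 2 | 3 | 4 | 5 | 6 | 7 | 8 |
|---|---|---|---|---|---|---|---|---|
| Probability | 0.485 | 0.242 | 0.129 | 0.073 | 0.040 | 0.020 | 0.008 | 0.002 |

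Every block has at least one certain place, and 52% of blocks have two or more.

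**Upper bound, exact arm.** Each arm has 4 places against 8 others, so the expected closing run is 3 × 4/9 = 1.333 per block. That is 1.333/12 = 11.1%, and 1.333 × 20 = 26.7, about 27 patients.

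**Gain in guessing.** With a full tally, always guessing the type with more places left is right 71.7% of the time. Always guessing web, with no tally, is right 66.7% of the time (8/12).

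**Sensitivity to delay.** If j other patients are randomised between this patient's invitation and randomisation, the assignment is certain at invitation only when the closing run is longer than j. The share is then the expected excess of the run over j, divided by 12.

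| j | Expected excess | Share |
|---|---|---|
| 0 | 2.044 | 17.0% |
| 1 | 2.044 − 1 = 1.044 | 8.7% |
| 2 | 1.044 − 0.515 = 0.529 | 4.4% |
| 3 | 0.529 − 0.273 = 0.257 | 2.1% |

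The subtracted terms are the probabilities of a run of at least 1, 2 and 3. The last line is calculated from unrounded values.

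**Sensitivity to pooling.** Suppose that each therapist sees only their own patients, patients are split at random with equal probability, and block boundaries are known. In a simulation of 20,000 blocks the certain share was 0.9% with two therapists, 0.2% with three, 0.05% with four, and nil to the precision of the simulation with eight or more. The article does not state the number of therapists.

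**The case against.** The strongest reply is that 17% needs three conditions together, and the article establishes none of them: that therapists know the block size and boundaries, that they hold a complete tally across all therapists, and that nobody else is randomised in between.

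- **Pooling.** The weekly supervision concerns web-based CBT, which wait-list patients do not receive, yet a complete tally needs wait-list allocations too. The result is described as readable at the patient's own randomisation, not in a log open to all therapists.
- **Delay.** For patients who take time to decide, the week before the telephone call makes an intervening randomisation quite possible.
- **Room to steer.** Fatigue and disability entry use fixed cut-offs, the MINI is structured, and an assistant operates the system.
- **Omission.** The full protocol may describe concealment that an article leaves out.

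Most of this stands, and it is why the figure must be read as a ceiling. A reader might infer that about one in six assignments can in fact be deduced before the patient is invited, or that therapists do steer patients. The documents support neither.

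The reply does not remove the point. Patients who decide at once are randomised at the session at which they were invited, so delay does not protect them. Group supervision makes sharing possible, even if it does not show it. The article itself prints the block size, so a therapist who reads it while recruitment is open knows it. The psychiatric judgement, the invitation and its timing remain open to influence despite the fixed cut-offs. The single block size and the visibility of results to the inviting therapist are stated design choices and not omitted detail.

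**Conclusion.** The point holds as a avoidable weakness in allocation concealment, not as a demonstrated bias. With one fixed block of 12 at one centre and no stratification stated, the share of web-versus-wait-list assignments that could be deduced before randomisation lies between almost nothing and 17% (2.04 per block, at most about 41 of 240). For the exact arm the ceiling is 11.1%, about 27 patients. The upper end assumes known block size and boundaries, fully pooled allocations and no intervening randomisation. The lower end, below 1%, applies if two or more therapists each see only their own patients. The article does not allow a choice within this range, because it is silent on what therapists knew and shared. The change is worth making because it is cheap and because the trial relies on self-report, a visible wait-list control and a single baseline covariate.

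**What to change.** For the allocation list, or its remaining part if recruitment has begun, replace the fixed block of 12 with randomly varying permuted blocks in multiples of three, for example 6, 9, 12 and 15. Withhold the sizes from therapists and administrative assistants until recruitment ends, and say so under Randomization and blinding in place of the current sentence. Withholding is essential: if the size were known, the same formula gives certain shares of 28.9% for blocks of 6 and 21.4% for blocks of 9, which is worse than 17.0% for 12. If the full protocol already varies and conceals the sizes, only the article's sentence needs correcting.

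Recording eligibility before the allocation is requested would not be a substitute, because a predicted arm can influence the invitation before that step.

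The cost is one new computer-generated list in the existing web system. The sample size and treatment are unaffected. The small downside is a possible slight imbalance in arm sizes if recruitment stops mid-block.

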### Statistical analysis

To determine whether web-based CBT leads to a reduction of fatigue severity compared to a wait list condition ANCOVA will be used. The second assessment of the primary outcome measure fatigue severity is the dependent variable in this analysis, with baseline CIS score as covariate, and condition as fixed factor. In RCTs ANCOVA yields greater power than other statistical methods [37]. Analyses will be based on intention to treat. Multiple imputation using fully conditional specification will be used to handle missing observations. The number of imputations will be at least equal to the percentage of missing data of the outcome measure. The assumption is made that data are missing at random [38]. A priori contrasts will be defined for the factor condition comparing web-based CBT with *protocol driven feedback* versus wait list and *support on demand* versus waiting list. When statistical significant differences are found, a sensitivity analysis will be performed on the basis of different assumptions about the values of missing data.

For the secondary outcome measures disabilities, physical functioning, psychological distress and the proportion of patients with clinical significant improvement in fatigue severity, the same analysis will be repeated, but with the secondary outcome measures at the second assessment as dependent variable, and the scores of these measurements at baseline as covariate. Statistical significance will be assumed at p < 0.025 (.05 corrected for two comparisons: web-based CBT with protocol driven feedback versus waiting list and web-based CBT with support on demand versus wait list) for the analysis of the results with respect to the primary outcome measure fatigue and p < 0.05 for secondary outcome measures. We will use a chi-square test to determine if the proportion of patients with a clinical improvement outcome significantly differ between treatment arm and wait list condition. We will also use ANCOVA to explore possible differences between the two web-based CBT formats with fatigue severity as dependent variable, baseline score as covariate and condition as fixed factor. Mean therapist time needed per patient in each web-based CBT format will be compared with an independent samples *t*-test and using bootstrapping when the therapist times are too skewed.

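### The numbered allocation label that patients can read risks disclosing the second web-based format, which the same paragraph says they will not be told about

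*Protocol article*

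**What the plan says.** All of the relevant text on labels and masking is in one paragraph of the protocol article, Randomization and blinding.

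- **What is displayed.** Once randomization is done, therapists and "patients will be able to read the randomization result on the screen i.e. ‘1) Internet therapy’ or ‘2) Internet therapy"; the third possible result is wait list. The two web results carry a digit; the wait-list result does not.
- **The safeguard.** "Patients will not be informed that there are two web-based CBT treatment conditions".
- **The reason for it.** "Knowledge of the two different treatment arms could affect the behaviour of the patient while following the web-based CBT".
- **A supporting step.** At the second intake session the therapist says that "the therapist will be available to support them during the web-based CBT without specifying the frequency of support". Instructions on how and when contact takes place appear only inside the application, after randomization.
- **Two routes to randomization.** Patients who want time to decide are contacted a week later: "An administrative assistant will call the patient and will perform randomization during this phone call". Patients who decide at once are randomized at the second intake session: "This will be performed by an administrative assistant in the presence of the therapist and patient".

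**The concern.** The plan sets a safeguard, gives a reason for it, and describes a patient-facing display that works against it. A patient who reads a numbered Internet result may wonder what the number stands for and suspect, or ask about, another version. The therapist in the room knows the allocation and will deliver the treatment, so a question about the number leaves that therapist either to disclose or to evade.

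At stake is the comparison between the two formats. They differ in how contact is triggered: a schedule with reminders in one, the patient's own request in the other. In the support-on-demand arm, the decision to ask for help determines how much support the patient receives and contributes to therapist time. A patient who suspects that another version exists might ask for help more often, or less, than one who does not. This is the kind of change in behaviour that the protocol names as its reason for withholding the information.

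**Working it through.** No calculation decides this point. The check is to set the statements side by side and ask what a patient could learn, by which route, and which analysis it could touch.

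**1. What the digit is for.** There are three possible results, and only two carry a number. If the digits simply numbered the options, wait list would have one too. Their only function is therefore to tell the two web arms apart. Staff need that information; under the safeguard, the patient does not.

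**2. What a patient learns from it.** The labels are joined by 'or', so the text describes a patient reading his or her own result, not the full list. Both web labels say Internet therapy, and neither says how the formats differ. The digit can suggest that a second Internet arm exists. It does not convey that one arm has scheduled contact and the other contact on request.

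**3. Who sees it.**
- In-person route: the patient is present when the result appears, so exposure is likely.
- Phone route: the assistant randomizes during the call. No view of the screen is described, nor are the words used to give the result.
- Bound: 240 patients over three arms is 80 per arm, so the two web arms hold 2 × 80 = 160 patients. The split by route is not stated, so the number exposed lies between 0 and 160. This is a bound, not an estimate.

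**4. Whether exposure is unbalanced between arms.** The route depends on whether the patient needs time to think, which is settled before allocation. Randomization therefore balances route across arms in expectation, and both web arms carry a digit. Exposure may differ by route, but that does not make it differ by arm.

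**5. Which analyses it touches.**

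| Comparison | Status in the article | Bearing of the cue |
|---|---|---|
| Each web format against wait list, fatigue severity | Primary, two a priori contrasts | Little: patients know in any case whether they received therapy or are waiting |
| Format against format, efficacy | Exploratory, although stated as the third hypothesis | Direct: knowledge of the other format is what the safeguard withholds |
| Format against format, therapist time | Planned comparison of means | Direct: requests for help drive support in the on-demand arm |

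The primary status in the first row rests on Statistical analysis, where "A priori contrasts will be defined for the factor condition comparing web-based CBT with" introduces each format against wait list.

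**6. Stated figures.** None depends on the label. For the exploratory comparison, 68 patients per arm, 80% power and two-sided 0.05 give a detectable standardized difference of 0.484, against the stated 0.48. That figure and the 80 per arm stand whatever the patient is shown.

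**The case against.** The strongest reply is that the text promises only that patients will not be informed of two conditions, and a bare digit does not inform them. A lone 1 or 2 may pass as a list number. The supporting steps also remain: support frequency is not specified at intake, and contact instructions appear only after randomization. Nowhere does the text say that a patient is told what the other format offers. The efficacy comparison most exposed is labelled exploratory, and the Discussion already warns that only a considerable difference could be detected.

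Most of this stands, and it limits the point. Three stronger readings that a reader might infer are not supported:

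- **That the label reveals the second format and defeats the safeguard.** The patient is described as reading one result, the digit is not explained, and the difference between the formats is not shown. Disclosure is a risk, not an established fact.
- **That uneven exposure by route biases the comparison between arms.** Route is fixed before allocation, so it does not unbalance the arms.
- **That the primary result is compromised.** Those contrasts are open to patients by design.

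The reply does not remove the inconsistency. The digit gives the patient no useful information, it separates exactly the two arms whose separateness is to be withheld, and the protocol itself regards that knowledge as able to alter behaviour.

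**Conclusion.** The concern holds as a minor inconsistency. A label readable by patients distinguishes the two web arms, while the same paragraph sets out to keep patients unaware that there are two. The number risks disclosing a second format to those who see the screen, chiefly those randomized at the second intake session. It is relevant to the exploratory format comparison and to therapist time. The primary contrasts are little affected, and the sample size, significance levels and analysis do not change.

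The size of any behavioural effect cannot be computed from the article, and its direction is not known. The conclusion assumes that the printed labels are those actually displayed and that patients randomized in person see them, as the text says. If the real screen shows patients an unnumbered label, the point reduces to correcting the description.

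**What to change.** - Give every web-arm patient the same unnumbered result, Internet therapy; wait-list patients get wait list. Use the same words on the screen and on the phone.
- Send the format code to the therapist separately, where the patient does not see it.
- State in Randomization and blinding what the patient is shown or told on each route.
- If some patients have already seen a numbered label, record which ones, so that exposure can be reported alongside the format and therapist-time comparisons.

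The cost is a label change in the randomization application, a sentence or two in the protocol and, if needed, one recorded item per patient. Arms, analysis and sample size stay as they are.
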